**Background**

Postoperative pulmonary complications (PPCs) are a significant factor influencing postoperative outcomes, leading to increased morbidity and mortality, prolonged hospital length of stay, and are closely associated with adverse financial healthcare outcomes.^1,2^ Patients undergoing cardiac surgery are particularly susceptible to PPCs, with cardiopulmonary bypass (CPB) being a major contributing factor. CPB induces a systemic inflammatory response and oxidative stress, resulting in pulmonary ischemia-reperfusion injury. Additionally, mechanical ventilation is typically interrupted during CPB, further exacerbating the risk of atelectasis. It is estimated that approximately 1.25 million patients worldwide undergo CPB-assisted cardiac surgery annually.^3,4^ PPCs remain prevalent following CPB cardiac surgery, with severity ranging from mild hypoxemia to acute respiratory distress syndrome (ARDS).^5^ Therefore, optimizing perioperative lung protection strategies to reduce the incidence of PPCs remains a critical area of research in cardiac surgery anesthesia and postoperative management.

Albumin is one of the most abundant proteins in human blood and plays a crucial role in various physiological processes beyond its colloid osmotic function. Its primary functions include the transport of hydrophobic molecules, maintenance of endothelial glycocalyx integrity, and multiple biological activities such as antioxidant, anti-inflammatory, enzymatic, and signal regulatory functions.^6,7^ Studies have demonstrated that albumin can suppress inflammatory processes, thereby reducing microcirculatory disturbances and tissue damage.^8^ In addition to serving as a marker of nutritional status, albumin is also recognized as a biochemical indicator of inflammation.^9^

Multiple studies have identified hypoalbuminemia as an independent risk factor for PPCs,^10,11^ Our previous retrospective study involving 660 elderly patients undergoing cardiac surgery with CPB also revealed that a preoperative albumin level below 40 g/L was an independent risk factor for PPCs in this population. However, high-quality studies evaluating the impact of albumin infusion during cardiac surgery on PPCs remain limited.

This study aims to evaluate the clinical effects of exogenous albumin infusion compared to 0.9% saline. The primary objective is to assess the efficacy of albumin infusion in reducing the severity and incidence of PPCs. The secondary objectives include evaluating the duration of postoperative invasive mechanical ventilation, the incidence of postoperative acute kidney injury (AKI), the occurrence of postoperative cardiovascular complications, the length of ICU stay, the total length of hospital stay, all-cause postoperative mortality, and changes in T-cell subsets as measured by flow cytometry. By comprehensively analyzing pulmonary, renal, cardiovascular, and hospitalization-related outcomes, this study aims to systematically assess the clinical value of albumin infusion in perioperative management.

**Methods/Design**

**Design**

This study is a prospective, single-center, randomized controlled pilot trial designed to compare the clinical effects of two different perioperative management strategies in cardiac surgery with CPB. The intervention group receives an intravenous infusion of 100 mL of 20% human albumin (Kilifor, Spain, 50 mL: 10 g) immediately after venous access is established, whereas the control group receives 100 mL of 0.9% NaCl solution.

This study adopts a standardized infusion protocol of 100 mL of 20% human albumin (20 g) based on several key considerations. First, previous studies have demonstrated that hypoalbuminemia (<40 g/L) is strongly associated with an increased risk of postoperative pulmonary complications (PPCs). Therefore, this study includes patients with preoperative albumin levels ≥30 g/L, aiming to elevate plasma albumin levels to approximately 40 g/L. Given that each 10 g of 20% albumin can transiently increase plasma albumin concentration by 3–4 g/L, a 20 g infusion is expected to raise levels to the target range, thereby optimizing postoperative recovery. Second, standardizing the infusion to 20 g ensures consistency in intervention, preventing confounding factors associated with individualized dosing adjustments, thereby enhancing the reproducibility and scientific rigor of the study. Additionally, high-concentration (20%) albumin effectively increases plasma colloid osmotic pressure, reducing tissue fluid retention, postoperative pulmonary edema, and perioperative fluid overload, which is particularly beneficial for patients undergoing cardiopulmonary bypass (CPB) cardiac surgery. Finally, considering the high cost of albumin and the need to minimize waste, as well as to maintain the integrity of the study’s double-blind design, a uniform administration of two vials (20 g) was implemented. This approach ensures that all participants receive the same dose, thereby optimizing perioperative management and allowing for a robust evaluation of the impact of albumin infusion on postoperative complications.Therefore, this study adopts this dose regimen to ensure both safety and efficacy, aiming to optimize perioperative management and evaluate its impact on postoperative complications.

**Study population**

**Inclusion criteria**

Adult patients were consecutively enrolled based on the following criteria: age ≥65 years; undergoing primary cardiac surgery, either alone or in combination with CPB, including coronary artery bypass grafting (CABG), valve repair or replacement, and aortic surgery; preoperative serum albumin level between 30-40 g/L; signed informed consent.

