**Standard Care**

All patients enrolled in the study received a standardized anesthetic protocol to minimize the potential impact of anesthesia on pulmonary outcomes. Radial artery cannulation was performed under local anesthesia, followed by tracheal intubation and mechanical ventilation. Mechanical ventilation was performed using a lung-protective strategy with volume-controlled ventilation, a tidal volume of 6–8 mL/kg ideal body weight, and an inspiratory-to-expiratory ratio of 1:2. The respiratory rate was adjusted to maintain an end-tidal carbon dioxide level of 35–45 mmHg. The inspired oxygen fraction (FiO₂) was initially set at 100% during tracheal intubation, then reduced to approximately 60% after intubation, and subsequently titrated to maintain peripheral oxygen saturation (SpO₂ ≥96%) during surgery. Positive end-expiratory pressure of 3-5 cmH₂O was applied as part of routine clinical practice. During CPB, mechanical ventilation was discontinued according to institutional routine practice and resumed after weaning from CPB. All patients received a standardized ventilation protocol throughout the procedure.Anesthesia was induced and maintained using target-controlled infusion (TCI) of propofol and remifentanil, with non-depolarizing neuromuscular blocking agents administered to maintain skeletal muscle relaxation. The bispectral index (BIS) was maintained between 40 and 60 to ensure an appropriate depth of anesthesia. Intraoperatively, the infusion rates of vasoactive agents and fluids were adjusted as necessary based on the patient’s hemodynamic status.

At the conclusion of surgery, patients were transferred to the cardiac surgery intensive care unit (ICU) while still intubated for postoperative management. All patients were immediately transferred to the ICU for continuous monitoring and respiratory and circulatory support. Extubation was considered only when the following criteria were met: the patient exhibited stable respiratory and circulatory function, regained clear consciousness, demonstrated the ability to comprehend and follow simple commands, restored adequate muscle strength, maintained a respiratory rate greater than 10 breaths per minute, and sustained oxygen saturation comparable to preoperative levels after breathing room air for 5 minutes.

All other treatments were administered in accordance with standard clinical care protocols.

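### As written, the inclusion criterion admits cardiac surgery without CPB, while the Design section defines the trial as surgery with CPB; the passages need reconciling

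*Protocol*

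**What the plan says.** **Who may enter.** Protocol, Inclusion criteria, admits patients "undergoing primary cardiac surgery, either alone or in combination with CPB", and goes on to list CABG, valve and aortic surgery with no on-pump qualifier. Protocol, Exclusion criteria, contains no item on off-pump surgery.

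**What the trial says it studies.** Protocol, Design, describes a comparison of "two different perioperative management strategies in cardiac surgery with CPB". The dose rationale in the same section ends on an oncotic effect "which is particularly beneficial for patients undergoing cardiopulmonary bypass (CPB) cardiac surgery".

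**Rationale.** Protocol, Background: "Patients undergoing cardiac surgery are particularly susceptible to PPCs, with cardiopulmonary bypass (CPB) being a major contributing factor", and "CPB induces a systemic inflammatory response and oxidative stress, resulting in pulmonary ischemia-reperfusion injury". The sponsor's own earlier data come from "660 elderly patients undergoing cardiac surgery with CPB".

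**Conduct.** Protocol, Standard Care: "During CPB, mechanical ventilation was discontinued according to institutional routine practice and resumed after weaning from CPB". No pathway for a patient without CPB is described, although the section says that the ventilation protocol was standardized for all.

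**Handling of CPB use.** Protocol, Randomization, gives 1:1 allocation and mentions no stratification. Protocol, Statistical Analysis, names subgroups by albumin level, age, sex and surgical type, but not by use of CPB.

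**The concern.** In the inclusion criterion, the word for surgery by itself is set against surgery combined with CPB. Its plain meaning is therefore surgery without CPB. Screening staff apply the eligibility text, not the Design paragraph, so the criterion decides who is in the trial.

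Two things are at stake. The first is interpretation: a mixed sample reported as CPB surgery would misdescribe its population, whatever the treatment effect. The second is sensitivity: if albumin works less well without the CPB insult, off-pump patients would pull the average effect toward zero in a trial of only 80 patients. The first follows from the text. The second is a possibility whose size the documents do not allow anyone to fix.

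**Working it through.** **Step 1. The passages side by side.**

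| Protocol section | CPB required? |
|---|---|
| Background | Rationale and prior cohort largely CPB-based; the closing objectives do not mention CPB |
| Design | Yes |
| Inclusion criteria | No, read literally |
| Exclusion criteria | Silent |
| Standard Care | Written as if always present |

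Nothing elsewhere in the protocol settles the matter.

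**Step 2. Reproduce the plan's figure.** Inputs from Protocol, Sample size: difference d = 0.3, SD σ = 0.45, two-sided α = 0.05, power 80%.

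Normal approximation: n per arm = 2 × (1.960 + 0.842)² × σ² / d² = 2 × 7.85 × 0.2025 / 0.09 = 35.3, so 36 per arm and 72 in total. The two-sample t-test version gives 36.3, so 37 per arm and **74 in total, as stated**. Dropout: 74 / 0.95 = 77.9, so 78 against the stated target of 80. No stated figure is in dispute here.

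**Step 3. Power at the planned size.** With 37 per arm, the standard error is 0.45 × √(2/37) = 0.1046. Power = Φ(0.3/0.1046 − 1.960) = Φ(0.907) = 81.8% (80.8% by the t-test).

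**Step 4. Illustrate dilution.** Let f be the off-pump share and r the off-pump benefit as a fraction of the on-pump benefit. The average difference is d(f, r) = 0.3 × (1 − f + f·r). Both f and r are assumptions. The SD is held at 0.45, and power is Φ(d(f, r)/0.1046 − 1.960).

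| f | r | Difference | Power, 37 per arm | Total N for 80% power |
|---|---|---|---|---|
| 0 | any | 0.300 | 82% | 72 |
| 10% | 0 | 0.270 | 73% | 88 |
| 20% | 0 | 0.240 | 63% | 112 |
| 30% | 0 | 0.210 | 52% | 146 |
| 10% | 0.5 | 0.285 | 78% | 80 |
| 20% | 0.5 | 0.270 | 73% | 88 |
| 30% | 0.5 | 0.255 | 68% | 98 |
| any | 1 | 0.300 | 82% | 72 |

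Totals are before dropout and use the normal approximation, hence 72 rather than 74 in the undiluted rows. Example: f = 20%, r = 0 gives 0.3 × 0.80 = 0.24, and Φ(0.24/0.1046 − 1.960) = Φ(0.334) = 63%.

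**The case against.** **It may be only a drafting slip.** The phrase could be a garbled way of saying that the listed procedures qualify singly or combined, all with CPB. Standard Care fits that reading. If so, no off-pump patient was intended and there is no dilution. This stands as a possibility, but it supports correcting the text, because the criterion as printed says something else.

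**The trial is not designed and justified only for CPB surgery.** A reader might infer that it is; the documents do not go that far. The objectives at the end of Background do not mention CPB, and the evidence gap is put in terms of cardiac surgery generally. CPB is called a major factor, not the sole one. Much of the case for albumin (endothelial glycocalyx, antioxidant and anti-inflammatory activity, correction of low albumin) does not depend on CPB. This objection stands and limits the point to the mismatch between sections.

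**The harm is not shown.** A reader might infer that off-pump patients will lower the event rate, add variability and shrink the effect. The documents give no off-pump share, event rate, variance or effect, and zero benefit is the worst case short of harm. This stands too: the power figures are conditional illustrations.

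**Power for PPC incidence is a separate matter.** One might start the dilution from the lower power for incidence (60% against 30%; about 75% at 37 per arm). The adopted sample size rests on the score, so the score is the right baseline here.

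**Conclusion.** The point holds as an internal contradiction. The eligibility rule admits surgery without CPB, the Design section defines a trial with CPB, Standard Care presumes CPB, and no exclusion resolves it. This is more than clerical, because following the rule as written could enrol patients outside the stated population.

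Its consequence for power is conditional. For off-pump shares of 10% to 30%, score power would fall from about 82% to between 73% and 52% with no off-pump benefit, or to between 78% and 68% with half the benefit. It would be unchanged with equal benefit or if no off-pump patient is enrolled. These figures rest on assumed shares and effects and on an unchanged SD. The documents do not support a claim that the result is diluted, nor that the sample size of 74 is wrong on this account.

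**What to change.** Reconcile Design, Inclusion criteria and Standard Care.

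- **If only CPB surgery is meant:** reword the criterion to primary cardiac surgery with CPB (CABG, valve repair or replacement, aortic surgery).
- **If off-pump surgery is meant to be eligible:** correct the population statement in Design and the ventilation description in Standard Care so that they cover both kinds of surgery. Report CPB use by arm, and add CPB use (treatment-by-CPB) to the subgroup analyses in Statistical Analysis. A main-effect covariate for CPB would not by itself address a different treatment effect off-pump. The objectives carry no CPB restriction and need no change. A 20% off-pump share would be only 0.20 × 80 = 16 patients, so this subgroup result could be no more than descriptive.
- **If enrolment is complete**, as the past tense of the eligibility text may suggest: state which rule was applied and report CPB use by arm. A new criterion could not change who was included.

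Cost: the first route is a one-line amendment that alters no stated sample-size figure, with possibly slightly slower recruitment if off-pump cases are common at the centre. The second needs a few lines in three sections and one more recorded variable in the analysis.

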**Exclusion criteria**

Exclusion criteria were as follows: history of allergy to albumin; preoperative use of high-dose positive inotropic agents, intra-aortic balloon pumps, extracorporeal membrane oxygenation (ECMO), or ventricular assist devices; preoperative renal insufficiency (serum creatinine ≥1.5 mg/dL) or dialysis dependency; left ventricular ejection fraction ≤40%; mechanical ventilation within 7 days prior to surgery; emergency procedures.

**Interventions**

The human albumin used in this study (manufactured by Grifols, Spain; 50 mL: 10 g) or the placebo (0.9% NaCl) was stored under sealed conditions to ensure stability and research integrity. To maintain the double-blind design and anonymity of drug allocation, all study medications were individually packaged in separate containers. Each participant’s assigned study medication was dispensed according to randomized enrollment numbers and was meticulously recorded in the case report form (CRF) to ensure data integrity and traceability.

The infusion of the study medication was administered intraoperatively, with the infusion initiated immediately after venous access was established. The medication—either human albumin or placebo—was delivered at a predefined rate, ensuring standardization and consistency in accordance with the study protocol.

**Standard procedures**

**Screening and inclusion**

During the preoperative visit, patients underwent screening based on the inclusion and exclusion criteria. If no exclusion criteria were met, patients were enrolled in the study after providing written informed consent.

**Randomization**

All patients who provided written informed consent were randomly assigned (1:1) to either the albumin group or the control group. Patient allocation was determined using a computer-generated randomization list, with the assignment sequence concealed from investigators to prevent selection bias.

**Blinding**

The trial was blinded for participants, meaning that patients were unaware of whether they were assigned to the albumin group or the control group. Additionally, blinding was applied to the responsible physicians, follow-up personnel, and statisticians. Upon the patient's transfer from the operating room, the ICU physicians remained unaware of the treatment allocation. Similarly, the research personnel responsible for follow-up and the data analysts had no knowledge of the patients’ group assignments, ensuring the integrity of the study.

**Procedure for unblinding if needed**

In the event of a serious adverse event requiring disclosure of the participant's group assignment, unblinding may be performed. The randomization list is securely maintained by an independent individual who is not involved in the study. In case of an emergency, investigators may contact the principal investigator, who is authorized to approve and coordinate access to the participant’s group assignment to ensure appropriate clinical management.

**Standard Care**

All patients enrolled in the study received a standardized anesthetic protocol to minimize the potential impact of anesthesia on pulmonary outcomes. Radial artery cannulation was performed under local anesthesia, followed by tracheal intubation and mechanical ventilation. Mechanical ventilation was performed using a lung-protective strategy with volume-controlled ventilation, a tidal volume of 6–8 mL/kg ideal body weight, and an inspiratory-to-expiratory ratio of 1:2. The respiratory rate was adjusted to maintain an end-tidal carbon dioxide level of 35–45 mmHg. The inspired oxygen fraction (FiO₂) was initially set at 100% during tracheal intubation, then reduced to approximately 60% after intubation, and subsequently titrated to maintain peripheral oxygen saturation (SpO₂ ≥96%) during surgery. Positive end-expiratory pressure of 3-5 cmH₂O was applied as part of routine clinical practice. During CPB, mechanical ventilation was discontinued according to institutional routine practice and resumed after weaning from CPB. All patients received a standardized ventilation protocol throughout the procedure.Anesthesia was induced and maintained using target-controlled infusion (TCI) of propofol and remifentanil, with non-depolarizing neuromuscular blocking agents administered to maintain skeletal muscle relaxation. The bispectral index (BIS) was maintained between 40 and 60 to ensure an appropriate depth of anesthesia. Intraoperatively, the infusion rates of vasoactive agents and fluids were adjusted as necessary based on the patient’s hemodynamic status.

At the conclusion of surgery, patients were transferred to the cardiac surgery intensive care unit (ICU) while still intubated for postoperative management. All patients were immediately transferred to the ICU for continuous monitoring and respiratory and circulatory support. Extubation was considered only when the following criteria were met: the patient exhibited stable respiratory and circulatory function, regained clear consciousness, demonstrated the ability to comprehend and follow simple commands, restored adequate muscle strength, maintained a respiratory rate greater than 10 breaths per minute, and sustained oxygen saturation comparable to preoperative levels after breathing room air for 5 minutes.

All other treatments were administered in accordance with standard clinical care protocols.

**Follow-up**

The follow-up period extends throughout the postoperative hospitalization, typically not exceeding 30 days.

**Blood Sample Collection and Flow Cytometry Analysis**

Arterial blood samples were collected from patients who provided informed consent for blood sampling and flow cytometry analysis at three time points: preoperatively, at the end of surgery, and 24 hours postoperatively. Blood sampling was performed via an arterial catheter, specifically before the infusion of albumin or saline, at the completion of surgery, and 24 hours postoperatively, to analyze the dynamics of Th1, Th17, Treg, γδ1, γδ17, and γδTreg cell populations.

During the experimental process, whole blood samples underwent erythrocyte lysis to remove red blood cells, thereby optimizing leukocyte isolation efficiency and minimizing interference from non-target cells. The isolated leukocytes were then subjected to sequential processing, including cell stimulation, viability staining, surface staining, and intracellular staining, ensuring the precise identification of different T cell subsets. Following staining, the cells were washed twice with PBS to remove unbound antibodies and dyes, and subsequently resuspended in PBS to preserve cell viability and signal stability. Data acquisition was performed using a FACS Fortessa flow cytometer (BD, San Diego, CA, USA) to ensure high-throughput detection accuracy and reproducibility.

The study utilized a comprehensive panel of antibodies targeting T cell subsets and cytokines, including APC-H7-CD3, BV605-CD4, BV421-TCRγδ, APC-IL-17A, BV510-IFN-γ, PE-Foxp3, PE-CY7-TGF-β1, BB700-IL-10, and isotype-matched control IgG. All antibodies were purchased from BD PharMingen or BioLegend (San Diego, CA, USA). The selection of antibodies was based on validated literature evidence to ensure specificity and sensitivity of the experimental results.

Flow cytometry data were analyzed using FlowJo software (BD, San Diego, CA, USA), employing a standardized gating strategy to ensure data accuracy, consistency, and reproducibility. To minimize potential bias during analysis, all flow cytometry data underwent independent quality control by at least two researchers, thereby enhancing scientific rigor and reliability.

**Study Endpoints**

The primary endpoints of this study are the severity and incidence of PPCs during hospitalization. The definition of PPCs is based on the scoring system proposed by Kroenke et al.,^12^ as detailed below.

Grade 1:

-Cough, dry

-Microatelectasis: abnormal lung findings and temperature > 37.5°C without other documented cause; normal chest radiograph

-Dyspnea, not due to other documented cause

Grade 2: (We only classified as grade 2 if two or more items in the grade 2 were present.)

-Cough, productive, not due to other documented cause

-Bronchospasm: new wheezing or pre-existent wheezing resulting in a change in therapy

-Hypoxemia (SpO₂ ≤ 90%) at room air

-Atelectasis: gross radiological confirmation (concordance of 2 independent experts) plus either temperature > 37.5°C or abnormal lung findings

-Hypercarbia (PaCO₂ > 50 mmHg), requiring treatment

Grade 3:

-Pleural effusion, resulting in thoracentesis

-Pneumonia: radiological evidence (concordance of 2 independent experts) plus clinical symptoms (two of the following: leucocytosis or leucopenia, abnormal temperature, purulent secretions), plus either a pathological organism (by Gram stain or culture), or a required change in antibiotics

-Pneumothorax

-Noninvasive ventilation, strictly applied to those with all of the following: Oxygen saturation (SpO₂) lower than 92% under supplemental oxygen; Need of supplemental oxygen > 5 L/min; Respiratory rate (RR) ≥ 30 bpm.

-Re-intubation postoperative or intubation, period of ventilator dependence (non-invasive or invasive ventilation) ≤ 48 hours

Grade 4: Ventilatory failure: postoperative ventilator dependence exceeding 48 hours, or reintubation with subsequent period of ventilator dependence exceeding 48 hours

Grade 5: Death before hospital discharge。

A PPC was defined as a PPCs score ≥3, with both the incidence and specific types of complications recorded accordingly. All patients underwent bedside chest radiographs on postoperative days 1, 3, and 5, followed by weekly imaging during hospitalization, unless otherwise indicated by the attending physician. All chest radiographs and follow-up assessments were independently analyzed by two trained researchers who were blinded to the study group assignments. The final PPCs score was determined only after ensuring consistency between radiographic findings and clinical manifestations. The scoring system ranges from a minimum of 0 to a maximum of 5.

Secondary endpoints include the duration of postoperative invasive mechanical ventilation, incidence of postoperative acute kidney injury (AKI), occurrence of postoperative cardiovascular complications, length of ICU stay, total hospital length of stay, and all-cause postoperative mortality.

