**Sample size**

Based on the published literature,^13,14^ and the results of the pre-test, we estimated that the difference in postoperative pulmonary complications scores between the intervention and control groups would be 0.3, with a standard deviation of 0.45. For postoperative pulmonary complications incidence, we assumed a rate of 60% in the control group and anticipated a 50% relative reduction in the intervention group. Using a two-sided test with a significance level (α) of 0.05 and a power of 80%, the required sample size was calculated separately for each outcome. The sample size estimation based on postoperative pulmonary complications scores resulted in a requirement of 74 patients, whereas the calculation based on postoperative pulmonary complications incidence indicated a requirement of 58 patients. To ensure sufficient statistical power, the larger sample size of 74 was adopted. Accounting for a dropout rate of 5%, the final recruitment target was set at 80 patients.

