**Statistical Analysis**

The baseline characteristics of patients will be summarized and analyzed using descriptive statistical methods. Normality will be assessed using the Kolmogorov-Smirnov test or the Shapiro-Wilk test. Normally distributed continuous variables will be presented as mean ± standard deviation (mean ± SD), whereas non-normally distributed continuous variables will be expressed as median and interquartile range (median [IQR]). Categorical variables will be reported as frequency and percentage (n, %). Group comparisons will be conducted using appropriate statistical methods based on the type of variable. Independent samples t-tests will be used for normally distributed continuous variables, while the Mann-Whitney U test will be applied for non-normally distributed continuous variables. Categorical variables will be compared using the chi-square test or Fisher’s exact test (for expected counts <5). Subgroup analyses were performed according to preoperative subgroup analyses for the PPC severity score, the primary continuous outcome of the study. Patients were stratified according to preoperative serum albumin levels (<35 g/L and 35–40 g/L) on the basis of the clinically relevant thresholds for hypoalbuminemia. Additional age, sex, and surgical type subgroup analyses were performed to evaluate the consistency of the treatment effect across different patient characteristics and procedures. A two-sided P value of less than 0.05 was considered to indicate statistical significance. All the statistical analyses and visualizations were performed using SPSS software version 25.0 (IBM, Armonk, NY, USA), Origin (OriginLab Corporation, Northampton, MA, USA), and GraphPad Prism (GraphPad Software, San Diego, CA, USA).

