For flow cytometry measurements at different time points, Mauchly’s test will be conducted to assess the assumption of sphericity. If the assumption is met, repeated-measures analysis of variance (repeated-measures ANOVA) will be used, followed by Bonferroni post hoc correction for multiple comparisons. If the assumption is violated, Greenhouse-Geisser correction or the Friedman test (for non-normally distributed data) will be applied. Additionally, the correlation between changes in T-cell subset counts and PPC scores will be analyzed using Spearman’s rank correlation test; Pearson’s correlation analysis will be used if the data are normally distributed. All statistical analyses will be conducted using two-sided tests, with a P-value <0.05 considered statistically significant. For multiple comparisons, P-values will be adjusted using Bonferroni correction. Data processing and visualization will be performed using SPSS 26.0 (IBM, Armonk, NY, USA), Origin (OriginLab Corporation, Northampton, MA, USA), GraphPad Prism (GraphPad Software, San Diego, CA, USA), and R 4.4.0.

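### Two primary endpoints are each sized and tested at two-sided 0.05, and the protocol does not say whether one or both must succeed

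*Protocol*

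**What the plan says.** - **Endpoints.** Protocol, Study Endpoints: "The primary endpoints of this study are the severity and incidence of PPCs during hospitalization". The aims paragraph that closes the Background also puts both under the primary objective. The binary endpoint comes from the same scale: "A PPC was defined as a PPCs score ≥3".
- **Sizing.** Protocol, Sample size: at two-sided 0.05 and 80% power, "the required sample size was calculated separately for each outcome". The score difference "would be 0.3, with a standard deviation of 0.45". For incidence, "we assumed a rate of 60% in the control group and anticipated a 50% relative reduction in the intervention group". The two results are 74 and 58 patients. The larger is adopted, and 5% dropout brings the target to 80.
- **Testing.** Protocol, Statistical Analysis, first paragraph: "A two-sided P value of less than 0.05 was considered to indicate statistical significance". The subgroup text there describes the severity score as the continuous primary outcome. It does not rank it above incidence.
- **Multiplicity.** The only such text is in the second paragraph of Statistical Analysis, on flow cytometry. It prescribes Bonferroni for the post hoc comparisons over time and later adds "For multiple comparisons, P-values will be adjusted using Bonferroni correction". That sentence comes just after one about all statistical analyses and does not state which comparisons it covers.

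**The concern.** With two primary endpoints, the meaning of a positive trial depends on a rule, and the sample size should follow from that rule. Here the endpoints and the alpha behind the sample size are fixed, but the rule is not. If one endpoint reaches P<0.05 and the other does not, the protocol cannot say whether the trial succeeded, and the choice would be made with the results in view. Each possible rule has a consequence that the sample size section does not recognise: a type I error above 5%, or power below 80%.

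**Working it through.** **Inputs from the protocol:** score difference 0.3, SD 0.45; incidence 60% against 30% (60% less a 50% relative reduction); alpha 0.05 two-sided; power 80%; 1:1 allocation; 74 patients (37 per arm); target 80, which after 5% dropout is 76 (38 per arm).

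**1. Reproducing the plan's figure.** For two means, n per arm = 2(1.96 + 0.842)² × (0.45/0.3)² = 2 × 7.85 × 2.25 = 35.3. The t-based solution is 36.3, so 37 per arm and 74 in total. This matches the protocol at unadjusted alpha 0.05, so no alpha was reserved for a second primary.

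**2. If either endpoint suffices.** Familywise error = 1 − P(|Z₁| < 1.96 and |Z₂| < 1.96). With independent tests this is 1 − 0.95² = 9.75%. Both tests use the same score, so they are positively correlated. The correlation is not given. Assumed values, from the bivariate normal:

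| Correlation | Familywise error |
|---|---|
| 0 (ceiling) | 9.75% |
| 0.5 | 9.1% |
| 0.7 | 8.3% |
| 0.9 | 7.0% |
| 0.95 | 6.5% |
| 1 | 5.0% |

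Simulation under the null fits this: 38 per arm, rank test on the score, chi-square test on grade ≥3. Four assumed grade distributions (8,000 trials each) gave 6.1%, 6.7%, 7.6% and 8.6%. Five others (5,000 each) gave 5.6% to 7.0%. One example to repeat: grades 0 to 5 with probabilities 0.10, 0.15, 0.15, 0.45, 0.10, 0.05, so 60% at grade ≥3, gave 6.7% in 8,000 trials. In the limiting case where every score is 2 or 3, the two tests coincide and there is no inflation.

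**3. If both must succeed.** The error does not exceed 5%, but joint power cannot exceed the power of the weaker endpoint. At alpha 0.05 and 37 per arm:
- Severity (t-based): 80.8%.
- Incidence (normal approximation): Φ{[0.3√37 − 1.96√(2 × 0.45 × 0.55)] / √(0.6 × 0.4 + 0.3 × 0.7)} = Φ{(1.825 − 1.379)/0.671} = Φ(0.665) = 74.7%. The exact chi-square calculation gives 74.2%.

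Joint power is therefore at most about 74%, and at least 0.808 + 0.742 − 1 = 55%. With all 80 patients evaluable, incidence power is 78.0% by the normal approximation, so the bound stays below 80%.

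**4. If Bonferroni were applied to the two primaries.** Alpha is 0.05/2 = 0.025 each. t-based severity power is then 71.8% at 37 per arm, 73.1% at 38 and 75.5% at 40. For 80%, n = 44.05, so 45 per arm and 90 patients, or 90/0.95 ≈ 95 with dropout.

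**The case against.** - **A statistical analysis plan may settle it.** Multiplicity detail is often held there, and that document is not shown. This stands for the detail. It does not remove what the protocol itself fixes: two primaries, each sized and tested at 0.05. A later plan that required both, or split alpha, would not fit the stated 80% power.
- **Nothing says that either endpoint is enough.** A reader might infer that the trial gives itself two chances of success, with a 9.75% error. The text does not support that. Taking the larger of the two sample sizes fits a wish to have both endpoints adequately powered at least as well, and 9.75% requires independence, which a score and its own cut cannot have. What stands is that no rule is fixed.
- **The Bonferroni sentence belongs to flow cytometry.** It sits in that paragraph and repeats a phrase used there for the post hoc tests, while the group comparisons have their own paragraph and threshold. This largely stands. The neighbouring sentence on all analyses leaves some doubt, so the power loss in step 4 is only conditional.
- **The incidence shortfall is not caused by Bonferroni.** This stands. At alpha 0.05, 74 patients already give about 74%. The usual formula needs 42 per arm (84 patients), not the stated 58, which is a separate matter.
- **The plan's inputs conflict.** With 60% at grade ≥3, the smallest SD an integer score can have is √(0.6 × 0.4) = 0.49, above 0.45. The severity power figures are therefore nominal.
- **It is labelled a pilot** (Design). It is nevertheless powered at 80% for efficacy and declares significance at 0.05. The label lowers the grade of the point but does not remove it.

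**Conclusion.** The point holds as an undefined success rule, not as proof that the trial's error rate is 9.75% or that Bonferroni removes its power. If either endpoint suffices, the familywise error is roughly 5.6% to 8.6%, about 1 to 4 points above nominal. That range rests on assumed grade distributions and shrinks towards 5% as the score approaches two adjacent grades. If both are required, joint power is at most about 74% at 74 patients, given the plan's 60% and 30%. If the Bonferroni sentence were extended to the primaries, severity power would be about 72% at 74 patients and 73% at 76, given the plan's 0.3 and 0.45. Should-fix, with moderate confidence.

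**What to change.** State one success rule in the protocol before unblinding. The cheapest is a fixed sequence: test the PPC severity score first at two-sided 0.05, and test PPC incidence (score ≥3) at two-sided 0.05 only if severity is significant. This holds the familywise error for the two tests at 5%. It also leaves the calculation of 74 and the target of 80 as they are, because severity drives that number. Add that the Bonferroni sentence covers the flow-cytometry comparisons only.

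The cost is wording, plus one real concession: incidence cannot be claimed if severity fails. Requiring both endpoints, or splitting alpha, would be equally valid, but each needs a new sample size. Parts of the protocol are in the past tense and the enrolment status is not stated, so the change should be dated and recorded as made before allocation is known.
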